### Methods in analysis to handle protocol non-adherence and any statistical methods to handle missing data {20c}

As suggested by the SPIRIT guidelines, we propose to test superiority using two analysis sets: the “intention-to-treat set”, considering all patients that are randomized regardless of whether they received the randomized treatment, and the “per protocol” set [49]. We propose declaring superiority of the experimental intervention only if shown superiority using both the “intention to treat” and the “per protocol” analysis set. As our study takes place in the ICU, it is expected that drop-outs will occur for medical reasons which make it unfeasible to continue in the study, but that are not related to the study itself. For this reason, there are two groups of participants who will be considered drop-outs. Firstly, any participant who can no longer continue in the study due to health reasons, before the first assessment for the primary outcome (i.e. the ICDSC) has been completed, will be considered a drop-out. Secondly, any participant for whom the neutral physician gave consent, but for whom the relatives withdrew consent, will be considered as a drop-out. Therefore, in order to maintain a sufficient sample size, it is important that these participants are replaced in a 1:1 manner, as approved by the local ethics committee. If a participant does drop-out of the study, their health status will be recorded at this point. As no long-term negative outcomes from the intervention are suspected, no further follow-up will be performed. If missing values occur within the dataset, we will use multiple imputation assuming missing data to be missing at random.

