### Who will take informed consent? {26a}

All patients who meet the inclusion criteria will be approached by a member of the study team within 24 h of ICU admission. However, since patients are often unable to give consent due to their condition and the situation of their relatives or authorized representative is often unclear at the beginning, a neutral physician may be consulted before the patient is included in the study. The neutral physician who is not involved in the study and who safeguards the participant interests provides a written authorization to enrol the patient.

If a proxy consent is not obtainable because no relatives and/or representative is identified or the representative cannot be reasonably contacted, the patient will stay in the study and their data will be used in order not to compromise the results of the study.

In the case where the patient is discharged from the ICU in a state of capacity that does not allow him/her to provide consent, a re-evaluation of their capacity to consent will only be done during the study follow-up visits or telephone follow-up calls (6 months visits). If the patient cannot provide informed consent at 6 months post-discharge, the relatives and/or representative will be asked again to provide informed consent to use the study data.

Informed consent will be obtained by a member of the study team after providing the patient, family member(s), or authorized representative with both verbal and written study information about what the study entails (e.g. its benefits, risks, design) and what the informed consent states. If the patient, family member(s), or an authorized representative agrees to participate in the study, they will be asked to sign a written consent form for their study participation. If a family member or authorized representative provides consent on the patients’ behalf, the patient will be asked directly for their consent as soon as their health condition allows. The patient will again be asked for their written informed consent 6 months post-ICU discharge to participate in a 6-month follow-up visit.

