Other pre-specified outcome variables include physiological parameters, feasibility of using the VR stimulation by ICU nurses, cognition at ICU discharge and 6 months post-discharge, health-related quality of life and functional independence before ICU admission and 6 months post-discharge, disease-related data, and survival 6 months post-discharge from the ICU. Physiological parameters (e.g. blood pressure, heart rate, respiration rate) will be recorded continuously and changes from baseline, or the start of an event such as VR stimulation, will be compared to later time points. The changes occurring in these parameters over time, together with disease-related data, are of interest and could indicate what effect, if any, VR stimulation has on the condition of the participant. Scores for health-related quality of life, functional independence, and clinical frailty before ICU admission and 6 months post-discharge, and cognition before ICU discharge and 6 months post-discharge, will be compared to determine if any significant differences occur. Additionally, the average survival 6 months post-ICU discharge will be compared between groups. Looking at these variables between groups is important as cognition, health-related quality of life, independence, frailty, and mortality, among others, are known to be negatively impacted by the presence of delirium during the time spent in the ICU. Therefore, it is meaningful to identify if there were any significant changes in these aspects for individuals in the treatment group compared to the controls. It will also be important to determine if providing such an intervention is feasible for the care providers. For this, the validated System Usability Scale will be completed by the nurses in order to understand if overall, the use of this technology was accepted and whether or not it could be integrated into standard ICU care practices [29].

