Cognitive impairment will be assessed by the study team before ICU discharge and 6 months post-discharge using the Montreal Cognitive Assessment [45]. The Montreal Cognitive Assessment has a known reliability of *κ* = 0.83 [45] and an established content validity in English and in French [45] and a sensitivity of at least 0.90 [46]. The average survival 6 months post-discharge will be obtained via a central database.

The study ends with a follow-up assessment 6 months after admission to the ICU. The study team interviews the participants during a regular follow-up session at the ICU. During the interview, the EQ-5D-5L, Functional Independence Measure, Clinical Frailty Score, and Montreal Cognitive Assessment will be administered. All assessments will be conducted according to the standard ICU care by trained ICU nurses.

In a final step following the VR intervention, the ICU nurse responsible for the intervention will be asked about the feasibility of applying the intervention, completing the 10-item System Usability Scale [29]. The System Usability Scale has a strong reliability score *κ* > 0.89 [47, 48] and an established construct validity, as well as concurrent validity (*r* = 0.86) [47, 48].

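### Missing-at-random imputation is optimistic for survivors whose cognition is too poor for the MoCA, and no sensitivity analysis is stated for them

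*Protocol article*

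**What the plan says.** All references are to the Protocol article.

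- **Missing data (item 20c).** The whole rule is: "we will use multiple imputation assuming missing data to be missing at random". It is not limited by outcome or by reason for missingness, and no alternative or sensitivity analysis is named.
- **Instrument (item 18a).** "Cognitive impairment will be assessed by the study team before ICU discharge and 6 months post-discharge using the Montreal Cognitive Assessment". For the 6-month assessment, "The study team interviews the participants during a regular follow-up session at the ICU".
- **Use (item 12).** Scores for "cognition before ICU discharge and 6 months post-discharge, will be compared to determine if any significant differences occur". Cognition is one of the other pre-specified outcomes, neither primary nor secondary.
- **Capacity (item 26a).** Some patients are expected to leave the ICU unable to consent, with capacity reassessed only at the 6-month contact. Some are expected to lack it still: "If the patient cannot provide informed consent at 6 months post-discharge, the relatives and/or representative will be asked again", and what is then sought from relatives is permission to use the data. For the visit itself, "The patient will again be asked for their written informed consent 6 months post-ICU discharge to participate in a 6-month follow-up visit".
- **Proxy answers (item 18a).** Relatives may answer for an incapacitated patient on the EQ-5D, the Functional Independence Measure (FIM) and the Clinical Frailty Score. No substitute, floor score or untestable category is given for the MoCA.
- **Population (item 10).** Acquired brain injury is eligible, and the alertness criterion is keeping the eyes open for 30 seconds.

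**The concern.** A relative cannot take the MoCA for the patient. If a living patient is too impaired to take it, the score is missing because of the value it would have had. That is missing not at random, and it arises in a group that the protocol itself expects.

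Imputation under missing at random predicts these scores from patients who could be tested and who look alike on recorded data. Among such patients, those who could not be tested are probably worse, so the predictions lean upward. Cognition is an outcome here because delirium is said to harm it. If VR prevents some delirium and, through it, some severe impairment, part of the benefit would appear as fewer untestable survivors. The stated rule weakens exactly that signal. Deaths before 6 months are a separate matter and are not counted here.

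**Working it through.** **Figures in the plan.** None is given for the MoCA, its spread or its missingness. The only figures used from the plan are the assumed delirium rates of 39% (control) and 30% (VR) in item 14. The 920 patients planned there concern the primary outcome and do not bear on this point.

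**Step 1: does the problem follow from the text?** Item 18a requires a test done with the patient, item 26a expects living patients without capacity at discharge and at 6 months, and item 20c covers every missing value with one assumption. The article does not say in words that untestable patients stay unscored. This follows from the absence of any other rule.

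**Step 2: formulas, with no informative covariate.**
- Overstatement of an arm mean = u × g, where u is the untestable share and g is the gap between the mean of testable and the true mean of untestable patients.
- Hidden difference between arms = (u_control − u_VR) × g.

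**Step 3: assumed inputs.** Tested patients average 24 and untestable patients would average 5 to 10, so g = 14 to 19. Take u_control = 10%. The overstatement of the control mean is then 0.10 × 14 = 1.4 to 0.10 × 19 = 1.9 points.

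**Step 4: untestable share under VR.** If delirium multiplies the risk of being untestable by R, and the planned delirium rates hold among survivors, then

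u_VR / u_control = [1 + 0.30(R − 1)] / [1 + 0.39(R − 1)].

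| Assumption | Ratio | u_VR | Hidden difference, g = 14 to 19 |
|---|---|---|---|
| R = 2 | 1.30/1.39 = 0.94 | 9.35% | 0.09 to 0.12 |
| R = 3 | 1.60/1.78 = 0.90 | 8.99% | 0.14 to 0.19 |
| Only delirious patients become untestable | 30/39 = 0.77 | 7.69% | 0.32 to 0.44 |
| Equal shares and gaps in both arms | 1 | 10% | 0 |

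The hidden difference is proportional to u_control. At 6% the three nonzero rows span 0.05 to 0.26 points; at 15% they span 0.14 to 0.66. A separate set of assumptions, 15% against 10% with g = 4 to 12, gives 0.05 × 4 = 0.2 to 0.05 × 12 = 0.6.

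**Step 5: scale.** Assume 300 survivors per arm and SD 4 within both testable and untestable patients. With 10% untestable, the variance is 16 + 0.10 × 0.90 × g², which is 33.6 (g = 14) to 48.5 (g = 19). The standard error of the difference is √(2 × 33.6/300) = 0.47 to √(2 × 48.5/300) = 0.57. The nonzero rows therefore hide about 0.09/0.47 = 0.2 to 0.44/0.57 = 0.8 standard errors.

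**Step 6: how much do covariates recover?** A simulation (200,000 patients, assumed mean 22 and SD 5, missingness rising as the true score falls, about 7.5% missing, true mean of the missing about 16.7) imputed scores from one covariate with correlation r to the score.

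| r | Mean imputed to the missing | Overall mean overstated by |
|---|---|---|
| 0 | 22.5 | 0.44 |
| 0.3 | 22.0 | 0.39 |
| 0.6 | 20.5 | 0.28 |
| 0.8 | 18.9 | 0.16 |

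Good predictors shrink the error but did not remove it: at r = 0.8, 0.16/0.44 = 36% remained. The inputs differ from those in Step 3, so this fraction shows the pattern only.

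**The case against.** **The imputation model may be rich.** A reader might infer that every untestable survivor is given an average testable score. The documents do not support that. Multiple imputation conditions on observed data, and the trial records the delirium checklist three times a day, consciousness and sedation, and proxy-capable FIM and frailty. Item 20c does not fix the model, which is normally left to an analysis plan. This stands, and it makes the figures in Step 4 upper values for their assumptions. It does not rescue the missing-at-random assumption itself.

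**Lack of capacity is not untestability.** A reader might infer that everyone who cannot consent at 6 months has no MoCA. Item 26a says that the patient will be asked and that capacity is reassessed at the follow-up visit or call, so such patients may be seen, and some could be scored. This also stands. The affected group is smaller than the group without capacity, and its size is unknown.

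**The 39:30 ratio is extreme.** Applying it to the untestable share supposes that only delirious patients become untestable, yet brain injury alone can do this. The 0.32 to 0.44 row is therefore the top of the range.

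**An analysis plan, or the deviation clause, may deal with it.** Detailed handling can be left to an analysis plan, but the article does not stay silent: it commits to missing at random without qualification. Item 20a allows departures when the data do not permit the planned technique. Imputation would run without any warning, so that clause would probably not be triggered.

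**The outcome is minor.** Cognition falls under a further objective that is descriptive, with no power claim. This stands and limits the weight of the point.

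**Conclusion.** The point holds in a limited form. The single missing-at-random rule is optimistic for a group that the protocol foresees, so mean MoCA scores will tend to be overstated in both arms. Bias toward zero in the comparison is conditional: it needs VR to lower the untestable share, or the gap to differ by arm.

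With 10% untestable in control and a gap of 14 to 19 points, about 0.1 to 0.4 points are hidden before covariate recovery, and none if shares and gaps are equal. Every input except the two delirium rates is assumed, so these figures show scale and are not estimates.

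A reader might infer that the trial's main result is compromised. It is not: delirium incidence does not depend on the MoCA. What is affected is the conclusion that can be drawn about cognition.

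**What to change.** 1. At ICU discharge and at 6 months, record why each MoCA is missing: untestable for cognitive reasons, refusal with capacity, lost contact, or other. Lack of capacity to consent should not by itself count as untestable.
2. Report the share untestable for cognitive reasons by arm.
3. In item 20c, limit reliance on missing at random to reasons unrelated to cognition, and include delirium duration, proxy FIM and frailty in the imputation model.
4. Pre-specify one sensitivity analysis for cognitively untestable survivors: either lowest rank with a rank-based or proportional-odds comparison, or delta-adjusted imputation over a stated range. The lowest rank is itself an unverifiable assumption, so it is proposed as a sensitivity analysis and not as the main one.

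The cost is one data field and one extra analysis, with no added visit or procedure. The reason should be recorded when the test is missed, because it is hard to recover reliably later.

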### Plans to give access to the full protocol, participant-level data, and statistical code {31c}

We will ask patients to provide informed consent for sharing their anonymized data. Once the study results as outlined in this proposal are published, we will make the de-identified study dataset available for secondary analyses by sharing the dataset upon reasonable request.

## Oversight and monitoring

### Composition of the coordinating centre and trial steering committee {5d}

The study will be monitored by an independent internal monitor. The monitor will evaluate the primary and secondary outcomes for completeness and correctness as outlined by the study protocol. Any decisions needing to be taken regarding the study will be done with the consensus of the entire study team and the relevant study authorities will be notified.

### Composition of the data monitoring committee, its role, and reporting structure {21a}

The study will be internally monitored according to the Good Clinical Practice directive and the monitoring and data verification plan, including the documentation of informed consent of study participants. Internally implies that the monitor is employed at the Department of Intensive Care Medicine, University Hospital of Bern (Inselspital), but carries out the monitoring independently, as they are neither involved in the study-specific processes (recruitment, study data collection, study interventions, or evaluation) nor in patient care. In their employment, they are administratively and functionally independent from the nursing and medical sector of the department.

### Adverse event reporting and harms {22}

In the scope of this study, no serious adverse events or adverse events are expected. Due to the serious condition of critically ill patients, adverse events will only be reported in the medical record if they are related to the VR intervention. Serious adverse events assessed with a causal relationship to VR will be reported to the ethics committee by the investigator and sponsor-investigator within 15 days.

### Frequency and plans for auditing trial conduct {23}

For quality assurance, the sponsor, the ethics committee, or an independent intern study monitor may visit the research site. Direct access to the source data and all study-related files is granted on such occasions. All involved parties will be required to keep the participant data strictly confidential.

### Plans for communicating important protocol amendments to relevant parties (e.g. trial participants, ethical committees) {25}

Substantial changes to the study setup and study organization, the protocol, and relevant study documents will be submitted to the ethics committee for approval before implementation. Under emergency circumstances, deviations from the protocol to protect the rights, safety, and well-being of human subjects may proceed without the ethics committee’s prior approval. Such deviations shall be documented and reported to the ethics committee as soon as possible. A list of all non-substantial amendments will be submitted once a year to the competent ethics committee together with the annual safety report.

### Dissemination plans {31a}

The results of the present study will be submitted for publication in peer-reviewed journals and will be presented at national and international scientific meetings. Currently, there are no known publication restrictions foreseen. The dataset will be available upon reasonable request once results have been published.

## Discussion

One challenge we will face during this study is the unpredictable reaction of patients to the VR stimulation when they are in a state of delirium. As such, the feasibility of providing VR stimulation to participants when they are already in a state of delirium is unknown. This can specifically be a problem due to their increased motor activity if they are in hyperactive delirium. Furthermore, there is a risk that delirious participants will not tolerate wearing such a head-mounted display and headphones and may even try to remove the items themselves. This may become a limitation in participant recruitment, as it does occur that patients enter into a state of delirium shortly after ICU admission. The study team will continue to provide the stimulation for as many days, and as consistently as possible; however, participant safety and comfort is the priority and, therefore, this aspect of unpredictability remains.

There currently remains the open question as to what specific aspect of the VR may be responsible for the effect we see, if any. Specifically, it is not known if it is the combination of audio and visual input, or the one or the other alone that creates an effect. Alternately, it could be that using these devices allows the patient to avoid noise overstimulation by using headphones and visual overstimulation by using the headset. This remains an open question.

It should be kept in mind that a limitation of the current study is the sparse literature confirming the reliability and validity of the questionnaires listed above, specifically for use in a language other than English and for our target group of ICU patients. The reliability and validity of the measures listed earlier are largely based on English speakers across a variety of patient populations and healthy controls. Therefore, we acknowledge that these values may not hold true, and applying it to participants in a language other than English may result in bias being introduced. Regarding the validity of the ICDSC, which we use for our primary outcome, the validity for the German version has not been assessed. Because of this, we will cross-check the score of the ICDSC with the Richmond Agitation Sedation Scale score. A positive Richmond Agitation Sedation Scale score is an important indicator of delirium based on symptoms that keep patients in the ICU, and therefore, should correspond to the ICDSC score.

## Trial status

Protocol version 2.0 (May 02, 2020)

Recruitment is expected to begin in March 2021 and continue until March 2024.

## Data Availability

The dataset will be available upon reasonable request once the results have been published.

## Abbreviations

REDCap: Research Electronic Data Capture System
ICDSC: Intensive Care Delirium Screening Checklist
ICU: Intensive care unit
VR: Virtual reality
